### Randomization

After the fourth author confirms the eligibility of the couples using the eligibility criteria, the method of generating the random allocation sequence (e.g., computer-generated random numbers) will be conducted using www.randomization.com by the first author. Each couple will receive a number from 1 to 42 to randomly allocate them into the A, B, or C group based on the randomization list.

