### Participants and setting

Participants will be couples undergoing infertility treatment at the Yazd Reproductive Sciences Institute, Yazd, Iran. This setting provides various medical and psychological facilities for couples undergoing infertility treatment. Recruitment will take place at the Yazd Reproductive Sciences Institute by the first and fourth researchers who will assess the eligibility criteria. Participants data will be kept confidential in this study.

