### Blinding

No blinding will be performed in this study because couples will be aware of their intervention method.

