### Intervention

Interventions will be conducted by the first author, who has a certificate in midwifery counseling, under the supervision of the second and third authors. All three interventions groups will receive five weekly intervention sessions (one session per wk) in a combination of threeone-hrface-to-face sessions (which they will attend at the Yazd Reproductive Sciences Institute in order to be visited by physicians, receive their drugs or do their medical tests, based on routine care at the Yazd Reproductive Sciences Institute) and two online sessions via telecommunication software (WhatsApp sessions showing clips and films, presenting Powerpoints, and having online video or call chats). All of the face-to-face intervention sessions will be held in the same place (in the Yazd Reproductive Sciences Institute) with similar counselors in the three groups. The same counselor will assess the couple's homework assignments in the three groups. A daily reminder will be sent to couples via short text messages or through WhatsApp.

#### Intervention group 1

The first intervention group (PERMA model) will receive counseling with the content of positive-oriented psychology (14). Positive psychology focuses on mental, individual, and social areas, including hope, optimism, happiness, honesty, patience, calmness, courage, loyalty, and wisdom. The PERMA model is applied to positive emotions, engagement, relationships, meaning, and accomplishment in couples. This model focuses on positive things such as good features, virtues, and human abilities. This can eventually lead to changes in lifestyle and attitudes (24) (Table I).

#### Intervention group 2

The second intervention group will receive IBCT counseling based on couple's therapy (21). In this method, couples are encouraged to have empathy and emotional acceptance in relationships, raise the threshold of tolerance in facing problems and improve problem-solving skills. This method teaches them to negotiate instead of judging, which can ultimately lead to positive changes in couples' behaviors (25) (Table II).

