## 3. Discussion

Nowadays, many couples face the challenge of infertility and the problems resulting from its treatment. Infertility causes stress and anxiety in infertile couples which affect their lives. Psychological problems also exacerbate infertility. Women undergoing infertility treatment with in vitro fertilization or other methods may experience a change in their quality of life, marital relationship, and sexual functions. Psychological interventions have a significant impact on reducing these problems of infertile couples (30, 31). The PERMA model is used to increase well-being and health (13), increase happiness, improve depressive symptoms (12), and increase personality strengths (32). The effect of behavioral therapy on infertile couples is significant, which enriches communication, increases marital satisfaction, protects relationships, and helps to solve problems (17). In the first phase of the present study, the content of the interventions' sessions was developed and adjusted based on a literature review and the opinions of expert panel members from various related disciplines. The intervention sessions will be conducted by trained and experienced counselors in all three groups. These packages can be used for raising optimism, increasing communication skills, and providing infertility treatment information to couples and other researchers.

There are five building blocks in the PERMA model that enable flourishing and improved mood. We have chosen this model to assess whether improving the mood, after practicing the domains of the PERMA model, can lead to amelioration of tolerance in couples and the mean scores of the FPI.

In the IBCT model, couples learn communication skills, problem-solving skills, behavioral exchange techniques, and empathetic joining. The communication training program leads couples to communicate better and improve their conflict-resolution skills. We expect improvement in communication skills to lead to improvement of the mean scores of the FPI.

Many patients with infertility who have psychological stress do not receive mental health services. Couples seeking infertility therapy should be informed about the treatment process because a lack of information leads to stress. Perhaps using an infertility treatment training program can reduce their stress.

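### The first author co-recruits couples, generates the allocation sequence and delivers the interventions, so the stated roles do not protect allocation from someone who enrols and treats

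*Protocol article*

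**What the plan says.** The protocol article spreads the first author's roles over three sections.

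- **Participants and setting:** recruitment is carried out "by the first and fourth researchers who will assess the eligibility criteria".
- **Randomization:** the sequence follows confirmation of eligibility by a colleague: "After the fourth author confirms the eligibility of the couples using the eligibility criteria", the generation step "will be conducted using www.randomization.com by the first author". Assignment from the resulting list is then described as follows: "Each couple will receive a number from 1 to 42 to randomly allocate them into the A, B, or C group based on the randomization".
- **Intervention:** "Interventions will be conducted by the first author, who has a certificate in midwifery counseling, under the supervision of the second and third authors".

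On masking, the Blinding section states: "No blinding will be performed in this study because couples will be aware of their intervention method". Under Data collection instruments, each spouse fills in the questionnaires separately, which covers the FPI and the satisfaction scale. Pregnancy is obtained from a single yes/no item. All outcomes are therefore reported by participants who know their arm.

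The article does not say who keeps the list, who gives out the numbers, or when the arm behind a number is revealed.

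**The concern.** Randomisation protects a comparison only if those who decide on a couple's entry cannot foresee or influence its arm. Here one named person helps find and screen couples, makes the list and then counsels the couples assigned from it. That person could know the next assignment while deciding whom to approach and when, or could affect the pairing of couples with numbers.

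The screening information makes this matter more. One exclusion criterion uses the FPI, which is also the instrument for the first primary outcome, so a couple's starting level on that outcome can be known at entry.

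At stake is the comparability of the three arms at entry. Baseline FPI is collected, so an imbalance on it can be seen and partly adjusted for. An imbalance on unmeasured features, such as motivation or quality of the relationship, cannot. Lack of blinding and self-report are separate sources of bias. They do not cause selection at entry, but they leave no masked or objective outcome against which a doubtful result could be checked.

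**Working it through.** The plan gives no figure on this point, so the check sets the sections side by side.

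**Roles as stated**

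| Step | Named person | Section |
|---|---|---|
| Recruit and assess eligibility | First and fourth researchers | Participants and setting |
| Confirm eligibility | Fourth author | Randomization |
| Generate the sequence | First author | Randomization |
| Hold the list, give out numbers, reveal the arm | Not stated | – |
| Deliver the interventions | First author | Intervention |

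**Two readings of the order of events**

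1. *The list exists while couples are still being recruited.* Its maker can know which arm comes next and is also a recruiter. Envelopes or a separate custodian, if the full protocol has them, would hide the list from others but not from the person who made it.
2. *The list is made only after eligibility is confirmed*, as the opening clause of the Randomization section allows. Foreknowledge at screening then shrinks or disappears. However, the list is made by someone who has already met the couples, and no rule fixes which couple gets which of the numbers 1 to 42. The pairing of known couples with numbers stays open to influence.

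The overlap therefore matters on both readings, by different routes.

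**Scale, under an assumed scenario**

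The document gives no information on how often, if ever, steering might occur. The following shows only how sensitive arms of 14 couples are.

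- Inputs: 14 couples per arm (Sampling and sample size). Assumed: *k* pairs of couples exchanged between two arms, all in the same direction, each pair differing by *d* SD in expected couple-level FPI; no baseline adjustment.
- Each exchange moves the two arm means by *d*/14 in opposite directions, so the shift in the contrast is 2*kd*/14 SD.
- Standard error of the contrast: √(2/14) = 0.378 SD.

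| *k* | *d* | Shift (SD) | Shift / SE |
|---|---|---|---|
| 1 | 0.5 | 2 × 1 × 0.5/14 = 0.071 | 0.19 |
| 1 | 1 | 2 × 1 × 1/14 = 0.143 | 0.38 |
| 2 | 1 | 2 × 2 × 1/14 = 0.286 | 0.76 |

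Adjustment for baseline FPI would remove part of any such shift. The table is not an estimate of bias in this trial.

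**The case against.** The strongest defence has four parts.

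- **The article is a condensed account.** Envelopes, a custodian or central release may well be in the full protocol, and their absence here is no fault. This stands, and the point does not rest on their absence. It rests on roles that the article does state, and none of those devices hides a sequence from its maker.
- **Eligibility is confirmed by someone else, apparently before the sequence is generated.** This stands in part. The fourth author's check limits the first author's freedom over whether a couple qualifies. It does not govern whom a co-recruiter approaches, or when, or which number a confirmed couple receives. The text also does not say that all 42 couples are confirmed before the list is made.
- **One provider across arms is a reasonable choice.** It keeps counsellor effects comparable, and delivery by the first author is not a defect in itself. It matters only in combination with recruitment and list generation. The Discussion speaks of more than one provider ("The intervention sessions will be conducted by trained and experienced counselors in all three groups"), so it is less certain that one person treats every couple. The Intervention section nevertheless names the first author ("Interventions will be conducted by the first author, who has a certificate in midwifery counseling").
- **The exclusion criteria are not simply matters of opinion.** The severity criterion is tied to a scored questionnaire, although no cut-off is printed, and the criterion on recent distressing events gives an example and a time window. The argument therefore does not depend on the criteria being subjective.

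A reader might also infer that the article contradicts itself on who determines eligibility. It does not: two people can assess and one can confirm. A reader might add that the analyst should be masked. That is a separate matter, commonly left to the analysis plan, and has no bearing on selection at entry.

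**Conclusion.** The point holds as a weakness in the stated division of roles. The first author is co-recruiter and eligibility assessor, generator of the sequence and provider of the interventions, in an open trial with self-reported outcomes. This arrangement permits knowledge of the sequence by someone who enrols and treats or, on the other reading of the order of events, influence over the pairing of couples with numbers. The fourth author's confirmation is a partial safeguard.

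A reader might go further and conclude that allocation is unconcealed, or that the first author keeps the list. The article says neither: it is silent on concealment and on custody. Nothing in it suggests any intention to steer allocation.

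The size of any bias cannot be measured from the document. The shifts of 0.07 to 0.29 SD shown above rest wholly on assumed exchanges and indicate only that, with 14 couples per arm, a few couples can matter. The conclusion assumes that the named roles are carried out as written. It would weaken if the full protocol gives generation and release of the list to someone else.

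**What to change.** Amend the Randomization section so that:

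1. a team member who neither recruits couples nor delivers the interventions generates and holds the list;
2. numbers 1 to 42 are given strictly in order of entry;
3. that person releases each assignment only after eligibility, consent from both spouses and the baseline FPI have been recorded for that couple.

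The second and third authors are named as supervising the interventions, so someone without that link is preferable if available. Baseline FPI before allocation is probably already implied by its use in screening; stating it makes the order checkable.

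The cost is one task reassigned within the team, a few lines of text and a small delay per couple while the assignment is requested. Sample size, visits and interventions are unaffected. If couples have already been randomised, the report should state who generated and held the list, who gave out the numbers and in what order.

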### Blinding

No blinding will be performed in this study because couples will be aware of their intervention method.

### Intervention

Interventions will be conducted by the first author, who has a certificate in midwifery counseling, under the supervision of the second and third authors. All three interventions groups will receive five weekly intervention sessions (one session per wk) in a combination of threeone-hrface-to-face sessions (which they will attend at the Yazd Reproductive Sciences Institute in order to be visited by physicians, receive their drugs or do their medical tests, based on routine care at the Yazd Reproductive Sciences Institute) and two online sessions via telecommunication software (WhatsApp sessions showing clips and films, presenting Powerpoints, and having online video or call chats). All of the face-to-face intervention sessions will be held in the same place (in the Yazd Reproductive Sciences Institute) with similar counselors in the three groups. The same counselor will assess the couple's homework assignments in the three groups. A daily reminder will be sent to couples via short text messages or through WhatsApp.

#### Intervention group 1

The first intervention group (PERMA model) will receive counseling with the content of positive-oriented psychology (14). Positive psychology focuses on mental, individual, and social areas, including hope, optimism, happiness, honesty, patience, calmness, courage, loyalty, and wisdom. The PERMA model is applied to positive emotions, engagement, relationships, meaning, and accomplishment in couples. This model focuses on positive things such as good features, virtues, and human abilities. This can eventually lead to changes in lifestyle and attitudes (24) (Table I).

#### Intervention group 2

The second intervention group will receive IBCT counseling based on couple's therapy (21). In this method, couples are encouraged to have empathy and emotional acceptance in relationships, raise the threshold of tolerance in facing problems and improve problem-solving skills. This method teaches them to negotiate instead of judging, which can ultimately lead to positive changes in couples' behaviors (25) (Table II).

#### Intervention group 3 (control)

This group is considered an active control group. They will receive information regarding various infertility treatment techniques in ART (22, 26). Necessary care during treatment, the success and failure rate of ART, treatment complications, and cost of treatment will be discussed (Table III).

### Outcomes

The mean scores of the fertility problems will be determined (assessed by the FPI) in the women, men and couples at the baseline of the intervention, at the end of the 5
${}^{\text{th}}$
 wk of the intervention, and one month after the termination of the intervention (in the 9
${}^{\text{th}}$
 wk) in the three study groups. Also, the mean score of satisfaction with the counseling method will be determined (assessed by the satisfaction questionnaire) in women, men and couples at the end of the 5
${}^{\text{th}}$
 wk of the intervention, and in the 9
${}^{\text{th}}$
 wk in all three groups. Occurrence of pregnancy will considered as a secondary outcome, defined as a positive pregnancy test, which will be assessed in the follow-up in the 12
${}^{\text{th}}$
 wk.

### Data collection

The data will be collected by questionnaires at the baseline of the intervention, at the end of the 5
${}^{\text{th}}$
 wk of the intervention (the end of the intervention), and one month after the termination of the intervention (in the 9
${}^{\text{th}}$
 wk). Determination of pregnancy frequency and percentage will be carried out in the 12
${}^{\text{th}}$
 wk (Figure 1).

####  Data collection instruments 

Each husband and wife will complete the study questionnaires separately. All questionnaires in the baseline assessment will be completed face-to-face, but at the end of the 5
${}^{\text{th}}$
 wk of the intervention and at the 9
${}^{\text{th}}$
 wk, they will be completed electronically.

#### 2.11.1.1. Demographic questionnaire

Age, occupation, level of education, cause of infertility, duration of infertility, duration of the marriage, and duration of treatment will be assessed at the baseline of the intervention.

#### 2.11.1.2. FPI

The FPI questionnaire was developed by Newton in 1999 to determine stress associated with infertility. This scale includes 46 questions across five domains (social concern, sexual concern, relationship concern, rejection of parenthood, and need for parenthood). Its reliability has been reported to be 87% Cronbach's alpha. This questionnaire is a 6-point Likert scale, from strongly disagree = 1 to strongly agree = 6. Higher scores imply more fertility problems (27). It will be assessed at the baseline of the intervention, at the end of the 5
${}^{\text{th}}$
 wk of the intervention, and in the 9
${}^{\text{th}}$
 wk in the three study groups.

#### 2.11.1.3. Satisfaction with the counseling method scale

This variable will be measured by the researcher-made scale (Cronbach's alpha 0.87) (28). It scores between 1 (the least satisfaction) to 10 (the most satisfaction), using the visual analog scale method (29). It will be assessed at the end of the 5
${}^{\text{th}}$
 wk of the intervention and in the 9
${}^{\text{th}}$
 wk in the three study groups.

#### 2.11.1.4. Pregnancy

Pregnancywill be determined with one closed-ended question (yes or no) electronically in the 12
${}^{\text{th}}$
 wk.

**Table 1 T1:** Content of the PERMA model intervention

**Sessions**	**Aim**	**Contents**
**1**	Positive emotions	The welcome session, explanation of rules and homework. Explanation of four key elements of emotional intelligence including management, perception, understanding, and using emotions regarding infertility. Happiness and life satisfaction are important subjects. Try to increase positive emotions about the past by forgiveness, about the present by physical pleasures and mindfulness, and about the future by hopefulness. Write down three things you experienced today that were fun and made you happy. Describe how you felt.
**2**	Engagement	Experience of flow in various activities by more concentration in the moment and increasing self-awareness. When time stops for you and you are completely absorbed by the task. Positive mental engagement and flow suppress mental ruminations regarding infertility. Write down three things you experienced today when all your attention was on something or someone and you were not aware of your surroundings. When the clock stops for you, when you lose consciousness, you are completely absorbed in your work. Describe how you feel.
**3**	Positive relationship	Positive and engagement are two elements to achieve well-being and positive relationships. Relationships are essential to well-being. More support and connectivity to others can promote a good purpose in life and meaning. This process is a valuable way to feel more positive. Kindness for others improves the feeling of well-being and increases capacity for love, compassion, empathy, teamwork, and cooperation. Positive relations involve participation and cooperation and so help us to avoid comparing ourselves with others, and promote comparing our diseases like infertility with couples who have children in an empathic way. Three things you experienced today where you had a positive experience with people. Only a very small part of being positive is related to isolation and loneliness. When was the last time you laughed out loud? When was the last time you felt indescribably happy? All of these happened alongside other people. By managing relationships and choosing the right people, we can have close and intimate relationships with those around us. Write down how you feel about these experiences. You can also practice kindness.
**4**	Meaning	Meaning is a feeling of belonging to the bigger community than the self by more socialization that produces a sense of meaning, such as through religion, family, and the community. Couples with infertility can create a better meaning of life with the help of other couples with infertility. Write down three things you experienced today that were important, significant, and meaningful to you personally. Write down how you feel about these experiences.
**5**	Accomplishment	Feeling of happiness regarding achievement, competence, and success in daily life. Review of gained positive things like having more support, empathy with another couple with infertility, successes in life or infertility treatments like the maturation of the oocyte, better sperm analysis test and things like these. Write down three things you experienced today when you were successful and thought you did a very good job and describe how you felt. Assessment of positive changes in thoughts, perceptions, beliefs, and emotions regarding fertility problems.
PERMA: Positive emotions, Engagement, Relationship, Meaning, Accomplishment		

**Table 2 T2:** Content of IBCT intervention

**Sessions **	**Aims**	**Content**
**1**	Familiarity and evaluation	The welcome session, explanation of rules and homework. Establishing communication and carrying out initial evaluation based on functional analysis to achieve a codified formulation and treatment plan including theme, polarization, and mutual trap. Training skills regarding active hearing and concentration in a spousal relationship especially regarding infertility and fertility problems.
**2**	Feedback session	Familiarizing members with the treatment model, building trust and hope, and providing appropriate coordination between the focus on the current problems of the couples and the history of their marital relationship (the initial attraction that couples had for each other, etc.), examining the strengths of the marital relationship and also determining the compatible differences between them, the degree of commitment of the couples to the relationship, providing treatment formulation to the couple and setting goals.
**3**	Strategies for acceptance	Using empathetic joining and unified detachment methods to provide patterns for couples to experience their dissimilarities differently so that couple problems become a device for greater intimacy between them. Seeing fertility problems as a way for connecting the couple with more empathy.
**4**	Strategies for creating tolerance	Pointing to the positive aspects of negative behavior, practicing negative behaviors in a therapy session, as well as self-discipline to prevent couples from trying to change each other. Using behavior exchange techniques and teaching communication skills.
**5**	Strategies for making change	Using behavioral change techniques and communication, problem-solving skills training to make changes in couples' behavior directly. Avoidance of running away from fertility problems and spending more time which each other. Reviewing of positive changes in couple's relationship for better management of fertility problems using IBCT skills.
IBCT: Integrative-behavioral couple therapy		

**Table 3 T3:** Content of infertility treatment training program

**Sessions**	**Aims**	**Content**
**1**	Introduce infertility and ART	Brief description regarding the definition of infertility and the causes of infertility which include both male and female factors. ART will be described. A brief explanation of IVF and ICSI etc. will be given to the couple. Treatment protocols will be explained. Necessary precautions will be described before the couple performs tests such as sperm analysis. Necessary training on exercise, physical activity, and diet will be given, if necessary.
**2**	Supplements and drugs	Guidelines for taking supplements in males and taking ovulation-inducing drugs before ART in females will be provided. Taking supplements and medications that physicians order will be described.
**3**	Treatment costs and drug side effects	Explanations about costs and insurance coverage, common problems that occur while taking medications, and side effects of medications.
**4**	Puncture of ovum, sperm processing and failure of treatment	The possibility of canceling treatment due to unsatisfactory female test results and sperm analysis will be explained. The probability of failure of treatment, sperm processing, and how to puncture the ovum will be provided in the form of educational videos via mobile phone.
**5**	Transfer method and post-ART care	Fertilization number of transferred embryos and transfer methods will be taught to couples through videos. Information on IVF failure and success rates per cycle and medication guidance for endometrial preparation for transmission will be provided. Post-ART care will be taught.
ART: Assisted reproductive technology, IVF: In vitro fertilization, ICSI: Intracytoplasmic sperm injection		

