**Materials and Methods:**

The content of the interventions was developed and adjusted based on a literature review and the opinions of experts. In this three-arm parallel randomized clinical trial, 42 couples undergoing infertility treatment will be allocated randomly into three groups (n = 14 couples/each). Group 1 will receive the PERMA intervention, group 2 will receive the IBCT intervention, and group 3 as the control group will receive an infertility treatment training program intervention. The primary outcome will be the fertility problems, which will be measured by completing a fertility problem inventory at baseline, as well as in the 5
${}^{\text{th}}$
 and 9
${}^{\text{th}}$
 wk as a follow-up. Another primary outcome, satisfaction with the intervention, will also be assessed in the 5
${}^{\text{th}}$
 and 9
${}^{\text{th}}$
 wk. The secondry outcome will be a positive pregnancy test at wk 12. The interventions will be conducted through a combination of face-to-face and online via WhatsApp.

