### Objects

The primary object is determining and comparing the mean scores of fertility problems in women, men and couples at the baseline of the intervention, at the end of the 5
${}^{\text{th}}$
 wk of the intervention, and one month after ending the intervention (in the 9
${}^{\text{th}}$
 wk) in the three study groups. The other primary outcome will be the mean satisfaction scores of the interventional method in women, men and couples at the end of the 5
${}^{\text{th}}$
 wk of the intervention and one month after the intervention (in the 9
${}^{\text{th}}$
 wk) in the three study groups. The secondary outcomes will be the frequency and percentage of pregnancy at the time of follow-up (in the 12
${}^{\text{th}}$
 wk) in the three study groups (Figure 1).

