### Inclusion criteria

The inclusion criteria will be: Iranian citizens; who are literate; have at least one smartphone and are Internet literate; have an infertility record in Yazd Reproductive Sciences Institute, Yazd, Iran; are an assisted reproductive technology (ART) candidate; and want to continue treatment at the Reproductive Sciences Institute.

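### Pregnancy is defined as a positive test but captured only by one unverified, undated electronic yes/no question

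*Protocol article*

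**What the plan says.** The Outcomes section of the protocol article gives the definition: "Occurrence of pregnancy will considered as a secondary outcome, defined as a positive pregnancy test". The abstract agrees: the secondary "outcome will be a positive pregnancy test at wk 12". The Objects section names the summary measure: "The secondary outcomes will be the frequency and percentage of pregnancy at the time of follow-up", given by study group.

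Section 2.11.1.4 (Pregnancy) gives the instrument: pregnancy will "be determined with one closed-ended question (yes or no) electronically", in week 12. It names no test result, medical record or respondent.

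Two other places bear on what is feasible. The inclusion criteria require that couples "have an infertility record in Yazd Reproductive Sciences Institute, Yazd, Iran" and that they wish to go on being treated there. The exclusion criteria already rely on the Institute's medical records to check drug use.

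**The concern.** Definition and instrument are both stated, and the instrument is the weaker of the two. A positive test is an event with a result and a date. A closed yes/no answer is a participant's statement about that event; by its form it carries no date, and the article describes no check on it.

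This matters more here than in many trials. The Blinding section says that there is no blinding, and the two primary outcomes (the fertility problem inventory and satisfaction) are self-rated. Pregnancy is the only outcome that could be recorded independently of what participants report. The Discussion and Conclusion also look to pregnancy rate when they speak of fewer treatments and lower costs. If pregnancy too rests on an electronic reply, couples who do not reply are lost for an outcome that the treating centre might hold on file. A misread question also goes straight into the result.

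**Working it through.** **Inputs.** 14 couples per arm, 42 in all, randomised by couple, and a 15% attrition allowance (Sampling and sample size; Randomization); chi-square for qualitative data at the 0.05 level (Statistical analysis). The article gives no pregnancy rate and no power for pregnancy, so there is no stated figure to reproduce.

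**Step 1: what the answer can mean.** The wording of the question is not given. The table assumes truthful answers and compares two possible wordings with the event of any positive test.

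| Course to week 12 | Any positive test | Answer if asked about pregnancy now | Answer if asked about any positive test |
|---|---|---|---|
| Positive test, still pregnant | yes | yes | yes |
| Positive test, lost before week 12 | yes | no | yes |
| No positive test | no | no | no |
| No reply | yes or no | missing | missing |

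The second row is classified correctly under one wording and wrongly under the other. The definition does not settle which is meant: the abstract places the test at week 12, Outcomes says only that it is assessed at that follow-up, and Objects speaks of the time of follow-up. The fourth row is lost under either wording, whereas a record would resolve it wherever a test was recorded.

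**Step 2: size.**
- One misclassified couple: 1/14 = 0.071, about 7 percentage points in that arm's rate.
- Non-response at the planning attrition: 0.15 × 14 = 2.1, so about two couples per arm. Between counting both as not pregnant and both as pregnant, the arm's rate moves by 2/14 = 0.143, about 14 points. Applying the 15% to the week-12 question is an assumption; the article states it only as a sample-size allowance.

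**Step 3: the unit of analysis, as a conditional check only.** Suppose both spouses' concordant answers were entered as separate persons. Every cell of the 3 × 2 table doubles, so the chi-square statistic doubles. The true type I error of the nominal 5% test (2 degrees of freedom, critical value 5.991) is then P(χ² > 5.991/2) = exp(−5.991/4) = 0.224. Simulation with 400,000 runs at each assumed rate from 20% to 50% gives:

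| Unit | Type I error |
|---|---|
| Couple (14 per arm) | 0.040 to 0.053 |
| Person, spouses counted separately (28 per arm) | 0.227 to 0.248 |

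For example, 3, 6 and 8 pregnancies of 14 give p = 0.153 by couple and p = 0.023 if each is counted twice. These figures show why the unit is worth one sentence in the plan. They do not describe what the plan says it will do.

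**The case against.** The strongest reply is that the two sections are compatible: Outcomes says what counts as pregnancy, and 2.11.1.4 says how the information is collected. If the question asks about a positive test, the recorded outcome is a report of the defined event and not a different outcome. That is fair, and it limits the point. The loss-before-week-12 example depends on wording that is not shown. What remains is that the report is unverified and undated under any wording.

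A second reply is that a condensed article may leave detail to the full protocol. That covers the handling of non-response and the denominator, which are not held against the plan here. It does not cover the instrument, because the article states one, and it is a single question.

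A reader might go further and infer that each pregnancy will be counted twice, because "Each husband and wife will complete the study questionnaires separately". The article does not support this. That rule is followed by completion arrangements for baseline and weeks 5 and 9 only. The Data collection section treats week-12 pregnancy in a sentence of its own. Objects and Outcomes split the inventory and satisfaction scores by wife, husband and couple, but not pregnancy. The chi-square sentence names no unit, and randomisation is by couple. Double counting is at most something that the text does not rule out.

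Finally, the article does not say that pregnancy tests are done or recorded at the Institute, so a record may not exist for every couple. This stands, and it is why the question should stay as a fallback.

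**Conclusion.** The point holds in a limited form. The plan defines pregnancy by a test and measures it by one unverified, undated electronic answer, so its potentially objective outcome becomes self-report. Each misclassified couple costs about 7 percentage points in an arm of 14. How many couples would be affected, and in which direction, cannot be derived from the article.

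The conclusion rests on reading the electronic question as answered by a participant, which is the natural reading of 2.11.1.4. It does not rest on double counting; the type I error of about 22% to 25% would apply only if spouses were counted separately. Pregnancy is a secondary outcome with no stated power, so this is a worthwhile, inexpensive improvement and not a threat to the primary comparison. It is best settled before data collection, since later analysis cannot fully recover results and dates that were never collected.

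**What to change.** Bring the definition and the instrument into line:

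- Define the outcome as any positive pregnancy test from randomisation to week 12.
- Take the result and its date from the Institute record where available.
- Use the electronic question only where no record exists, word it to ask about any positive test in that period and its date, and note the source of each result.
- Count one outcome per couple, with all randomised couples in the arm as denominator.

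An exact test for the small arms is optional. So is a sensitivity analysis of the week-5 and week-9 inventory scores by test date.

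The cost is a record look-up for 42 couples at the treating centre and a change of wording. The downside is that some couples may have no recorded test, so the outcome would come from two sources; reporting how many came from each, by arm, deals with that.
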